### Data Collection and Analysis

The same physicians (ophthalmologists and endocrinologists) and laboratory technicians will collect and evaluate the data from all patients. Data are recorded in questionnaires, images and electronic quantitations (OCT, fundus biomicroscopy and fluoroangiography), and laboratory biochemical determinations. All images collected during the study are sent for re-assessment to a central evaluation center at the recruiting Institution to insure accurate evaluation. The coordinator of the study will continually examine the registry to insure all collected data are complete, accurate, and valid. Data logically inconsistent will be confronted with information in external database. Data collected on formatted paper forms are entered into a computer and electronic registries carefully reviewed by a third party to identify missing data, invalid or erroneous entries, and inconsistent data. Any data review activity and remediation efforts will be documented. Statistical methods evaluate continuous and categorical variables, the association between hormonal levels and outcome, and the relative contribution of confounding factors. The study data will be stored in the recruiting Institute through private accessing codes and kept for up to 10 years following the publication of the study. The data information will then be destroyed.

### Safety Considerations

Levosulpiride is clinically approved and available in different countries (Italy, Spain, Germany, Belgium, Mexico, South Korea, etc). It is used at low doses (25–75 mg/day) as a prokinetic agent for the treatment of dysmotility-like functional dyspepsia (35, 36). It penetrates the blood–brain barrier poorly (37) so higher doses (800–2400 mg/day) are required for its use as an anti-depressant and anti-psychotic agent (38). Duration of treatment ranges from 1 week to more than 2 years (23). Low doses of levosulpiride are well tolerated during both acute and chronic administration. Heart rate and electrocardiogram are not altered (35) and sedation is rare (36). As the pituitary is outside the blood–brain barrier, low doses of levosulpiride increase serum PRL (39). Adverse effects of hyperprolactinemia include decreased libido, amenorrhea and infertility, breast engorgement and lactation, and gynecomastia (40). In a multicenter, double-blind, placebo-controlled trial of 408 dyspeptic patients receiving oral levosulpiride (25-mg TID for 4 weeks) the total incidence of hyperprolactinemia related disorders was 7% in female patients (41). More recently, a study in 342 dyspeptic female and male patients, using the same levosulpiride treatment, reported 40 patients (11%) with adverse effects (26.7% galactorrhea, 17.8% somnolence, 11% fatigue, and 11.5% headache), none of whom abandoned the study due to side effects (36).

### Current Status

Patients started enrolling in this trial on May 2016. As of January 2018, 270 patients were screened and 63 identified as candidates signed the informed consent. Later nine patients were excluded (1 due to hyperprolactinemia, 6 because of glomerular filtration rates <30 mL/min, 1 due to glaucoma, and 1 requiring laser therapy). From the remaining 54 study subjects, 9 dropped-out after randomization (3 did not comply with the study medication, 2 missed outcome data, 1 required conventional therapy, and 3 vitrectomies were rescheduled as patients forgot to take hypertension medication before surgery and had very high blood pressure values), and 45 completed the study. Relevant protocol modifications will be registered at ClinicalTrials.gov. The protocol last amendment was registered on October 3, 2017 and consisted in the inclusion of DME patients receiving placebo or levosulpiride on top of standard antiangiogenic therapy with ranibizumab.

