### Study Design

The study design is shown in Figure 1. This is a single-center, prospective, randomized, placebo-controlled, double-blind clinical trial on the efficacy and safety of levosulpiride for the treatment of DR and DME. An eight-armed study design is followed in which diabetic male and female subjects are selected from four different populations, those having DME, NPDR, PDR undergoing vitrectomy, and DME that will receive antiangiogenic therapy with ranibizumab. Ranibizumab is a humanized monoclonal antibody fragment directed against all forms of vascular endothelial growth factor (VEGF) approved as antiangiogenic therapy for DME (27). Immediately after baseline, each of the four groups is randomly split up into a subgroup that receives levosulpiride and a subgroup that receives placebo (lactose pill). Allocation is randomly assigned *via* computer-generated random numbers. The comparison of ophthalmologic and health outcomes between groups 1 and 2 (DME: placebo and levosulpiride) and groups 3 and 4 (NPDR: placebo and levosulpiride) will evaluate the efficacy and safety of the medication against DME and NPDR, respectively. Comparison between groups 7 and 8 (DME plus ranibizumab: placebo and levosulpiride) will investigate the benefits of levosulpiride treatment on top of standard antiangiogenic therapy with ranibizumab in advanced DME. Although anti-VEGF agents are the firstline therapy for DME involving the central macula, approximately 50% of the patients do not respond suggesting the contribution of other vasoactive and proinflammatory mediators (28). Vasoinhibins block the vascular effects of VEGF and of other cytokines present in the vitreous of DR patients (17, 18, 20, 29), implying that levosulpiride may extend and potentiate the benefits of the anti-VEGF therapy. The comparison of serum and vitreous PRL levels between the groups 5 and 6 undergoing vitrectomy (DR: levosulpiride and placebo) will serve as a proof of principle that PRL enters the eye to counteract disease progression. Blood samples are drawn immediately prior to surgery and before the induction of anesthesia.

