### Enrollment and Randomization

After potential participants have signed the informed consent, their eligibility is evaluated based on the inclusion/exclusion criteria (Figure 1). If eligible, their demographic characteristics, medical history, and physical examination are assessed; both eyes are evaluated for visual acuity [Early Treatment Diabetic Retinopathy Study (ETDRS) chart test], retinal thickness (non-invasive optical coherence tomography, OCT), and retinal microvascular abnormalities (fundus biomicroscopy and/or fluoroangiography). Laboratory tests are also carried out to determine circulating levels of PRL, glycated hemoglobin, alanine aminotransferase, thyroid-stimulating hormone, and creatinine (Figure 1). The evaluations confirm eligibility, allow for the distribution of patients, and set the baseline reference for treatment comparisons. DME is diagnosed by means of ophthalmoscopy and OCT measurements of central retinal thickness (30). Patients are classified as having NPDR and PDR according to the international clinical DR severity scale (31). DME and NPDR patients are randomized in a 1:1 ratio to receive levosulpiride (25-mg orally TID for 4 weeks) or placebo (lactose pill orally TID for 4 weeks). PDR patients requiring vitrectomy (due to non-clearing vitreous hemorrhage, tractional retinal detachment, and/or severe neovascular proliferation) are randomly split 1:1 to receive levosulpiride (25-mg orally TID) or placebo (lactose pill orally TID) 1 week before undergoing vitrectomy. Patients requiring antiangiogenic therapy for the treatment of clinically significant DME are randomized to receive levosulpiride (25-mg orally TID) or placebo (lactose pill orally TID) during the 12 weeks of standard ranibizumab intravitreal therapy (0.5 mg every 4 weeks) (Figure 1). In all groups, the study medication is taken on top of standard therapy for diabetes, blood pressure control, or other medical conditions. Specifically, this therapy includes metformin, sulfonylureas, dipeptidyl peptidase-4 inhibitors, acarbose, insulin, ACE inhibitors or angiotensin II receptor blockers, beta blockers, calcium antagonists, and/or diuretics, etc. In the case of adverse and intolerable effects of the study medication, the treatment is stopped and reported as a failure (32).

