#### Objectives

The objectives of the study are to evaluate the effect of prolonged exposure to PRL induced by levosulpiride on DME and DR progression, evaluate the effect of levosulpiride as a combination therapy with ranibizumab on DME progression, and whether the actions of levosulpiride occur *via* the intraocular incorporation of PRL and its conversion to vasoinhibins. Therefore, the primary endpoints of the study medication are changes from baseline of ophthalmologic parameters and of PRL and vasoinhibin levels in the vitreous.

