#### Secondary Outcome Measures

The secondary endpoints evaluate the safety of the study medication by measuring:
Blood pressureBlood glycated hemoglobinSerum glucoseSerum creatinineHyperprolactinemia-related side effects documented at each participant visit (32)Dopamine D2 receptor blocker side effects documented at each participant visit (32)

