### Sample Size

The proposed sample size (Figure 1) was calculated according to expected differences in visual acuity, the main parameter of visual function. Using the formula for mean differences and the reported changes in visual acuity (33, 34), we considered a difference of 10 letters in the ETDRS chart test between baseline and after intervention, a SD of 10, a power 1 − β = 80%, and a type-I error rate of 5%. For PRL and vasoinhibin level outcome, sample size is in accord to experimental models of DR and clinical experience (14, 15). As the study progresses, the study may need to accommodate a different sample size to obtain clinically relevant and statistically significant differences, access to eligible patients, elimination of patients, etc.

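### Eliminating randomised patients whose eye disease worsens enough to need conventional treatment selects on the outcome under study, and nothing in the article returns them to the comparison

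*Protocol article*

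**What the plan says.** - **Elimination Criteria.** Disease worsening that makes conventional treatment necessary is listed as a reason for elimination, beside non-compliance, withdrawal of consent, relocation and missing outcome data.
- **Current Status.** Of 54 subjects, "9 dropped-out after randomization (3 did not comply with the study medication, 2 missed outcome data, 1 required conventional therapy"; the other three were rescheduled vitrectomies. The report then says that "45 completed the study".
- **Objectives.** The first aim is to "evaluate the effect of prolonged exposure to PRL induced by levosulpiride on DME and DR progression".
- **Study Design.** Comparing the arms in groups 1 to 4 "will evaluate the efficacy and safety of the medication against DME and NPDR, respectively".
- **Primary and Secondary Outcome Measures.** The primary list holds acuity, OCT, fundus, angiography and hormone measures, with no event for needing conventional treatment. The secondary list opens with "The secondary endpoints evaluate the safety of the study medication by measuring" and then names blood pressure, laboratory values, and prolactin- or D2-related side effects.
- **Enrollment and Randomization.** For intolerable adverse effects, "the treatment is stopped and reported as a failure". No such sentence covers worsening.
- **Data Collection and Analysis.** The analysis text is: "Statistical methods evaluate continuous and categorical variables, the association between hormonal levels and outcome, and the relative contribution of confounding factors". It gives no rule for eliminated patients.

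**The concern.** A patient whose oedema or retinopathy worsens until conventional treatment is needed has progressed, and progression is the subject of the trial. Elimination puts that patient in the same class as someone who moved to another state. If eliminated patients leave the comparison, each arm is judged on those who did not fail, and the share removed depends on how well the assigned treatment works.

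If levosulpiride helps, more failures leave the placebo arm and its remainder looks too good. If levosulpiride harms the eye, more failures leave the levosulpiride arm and part of the harm disappears from the mean. Neither outcome list would show the loss as a count by arm. The article also treats two kinds of treatment failure differently without giving a reason: intolerance is reported as failure, worsening leads to elimination.

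The concern bears mainly on groups 1 to 4. Groups 5 and 6 have one visit, after a week, and their purpose is hormone levels. Groups 7 and 8 already receive ranibizumab.

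**Working it through.** **1. The article's own counts (Current Status).** 63 consented - 9 excluded = 54. Drop-outs: 3 + 2 + 1 + 3 = 9. Completers: 54 - 9 = 45. The disposition adds up. Drop-out is 9/54 = 16.7%; removal for conventional therapy is 1/54 = 1.9%, with arm and group not given. The patient needing laser therapy was among the 9 excluded before the 54 and is not part of this point.

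**2. Inputs for the size of the bias.**
- From Sample Size: SD 10 letters, type I error 5%, and "we considered a difference of 10 letters in the ETDRS chart test between baseline and after intervention". I use 10 letters as the true difference between arms.
- Assumed: change in letters is normal, the placebo mean change is 0, and a patient is removed at a loss of c letters or more, with the same c in both arms. The documents give no c, so I vary it.
- Assumed for power only: 15 per arm (120/8, equal arms) and a two-sided t-test.

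**3. Formula.** For a true mean m, the mean among patients kept is m + 10·φ(a)/(1 - Φ(a)), and the share removed is Φ(a), with a = (-c - m)/10.

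**4. Example, c = 10.**
- Placebo (m = 0, a = -1): 10 × 0.2420/0.8413 = 2.88; 15.9% removed.
- Levosulpiride, m = +10 (a = -2): 10 + 10 × 0.0540/0.9772 = 10.55; 2.3% removed. Difference: 10.55 - 2.88 = +7.7.
- Levosulpiride, m = -10 (a = 0): -10 + 10 × 0.3989/0.5 = -2.02; 50% removed. Difference: -2.02 - 2.88 = -4.9.

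**5. Range.** The first row sets placebo removal at 1/54, which corresponds to c = 20.9.

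| Cut c (letters lost) | Placebo removed | True +10 seen as | True -10 seen as |
|---|---|---|---|
| 20.9 | 1.9% | +9.6 | -7.9 |
| 15 | 6.7% | +8.8 | -6.3 |
| 10 | 15.9% | +7.7 | -4.9 |
| 5 | 30.9% | +6.3 | -3.7 |

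**6. Power.** With all patients kept, power is about 75% in either direction. By simulation after removal, power to detect the benefit is about 73%, 68%, 59% and 44% down the table. Power to detect the harm is about 61%, 44%, 26% and 11%.

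**7. The direction is not fixed.** Suppose 20% of levosulpiride patients average -20 letters and 80% average +5. The true mean is 0.2 × (-20) + 0.8 × 5 = 0, equal to placebo. With c = 10, the first subgroup keeps 15.9% of its patients (mean -4.75) and the second 93.3% (mean 6.39). The kept mean is (0.2 × 0.159 × (-4.75) + 0.8 × 0.933 × 6.39)/(0.2 × 0.159 + 0.8 × 0.933) = 5.93. Against placebo at 2.88, this is a spurious benefit of about +3 letters. The mixture is an assumption, chosen only to show that the sign can change.

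**The case against.** The strongest reply is that the article never says eliminated patients are left out of the analysis. The status section reports disposition and defines no analysis set, and a full protocol or SAP that is not shown could keep these patients. This stands as a limit: exclusion is the natural reading, not a stated fact. It is a strong reading, though. Elimination is listed beside missing outcome data, the Sample Size section names elimination of patients as a reason the sample size may change, and the patient concerned is counted outside the completers. The point is about a rule the article fixes, not about an analysis set it omits.

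A reader might infer more than the documents support:
- *That ocular harm would be invisible.* Outcome Measures has adverse events and primary outcomes documented at each visit, Blinding allows unblinding for marked deterioration, and Dissemination promises that all data will be communicated. None of these puts eliminated patients back into the efficacy comparison, but worsening up to elimination is recorded.
- *That benefit and harm are always understated.* This holds for a uniform shift with one threshold in both arms, which blinding supports. Step 7 shows that mixed responses can reverse it.
- *That the bias is known to be large.* The larger figures rest on assumed cuts that remove far more than the 1 of 54 reported. That rate is itself a weak guide, because it pools groups and arms at an interim date.
- *That the dropped patient certainly worsened.* The status section says only that conventional therapy was needed; the link to worsening comes from the elimination criterion.

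**Conclusion.** The concern holds in this form. The article sets an outcome-dependent reason for elimination, lists a patient who fits it as a drop-out, and nowhere returns such patients to the comparison. If elimination means leaving the analysis, groups 1 to 4 are compared on a set selected by progression.

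The size is unknown. Under the stated normal model with a uniform shift, it runs from slight for a benefit at the pooled observed rate (+10 seen as +9.6) to substantial at a 5-letter cut (+6.3). A harm of 10 letters is masked more at every setting, from -7.9 down to -3.7. These figures also assume that acuity alone triggers removal, whereas the actual decision may rest on OCT or clinical judgement. The documents do not support a claim that the results so far are materially biased: one patient is involved, in an unstated arm.

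**What to change.** State in the Elimination Criteria that elimination for worsening ends study medication, not inclusion in the analysis. Then:
- analyse each such patient in the randomised arm, using the acuity and OCT values recorded before conventional treatment;
- add a sensitivity analysis that counts these patients as failures, for example by worst rank;
- report the number needing conventional treatment by arm and population;
- include the patient already dropped, where pre-treatment outcome data exist.

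The cost is a wording change, one sensitivity analysis and one table. No added patients, visits or procedures are needed, and the two-weekly visits in groups 1 to 4 should usually supply a recent value. The downside is that the carried value precedes the planned final visit. The clinical decision to give conventional treatment is untouched.

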### Outcome Measures

After enrollment, four study visits take place every 2 weeks during a follow-up period of 8 weeks in groups 1 and 2 (DME: placebo and levosulpiride) and groups 3 and 4 (NPDR: placebo and levosulpiride). For groups 7 and 8 (DME plus ranibizumab: placebo and levosulpiride) enrollment is followed by three visits, one every 4 weeks (at the time of ranibizumab intravitreal delivery). At each visit, the medical history, physical examination, adverse events, and primary and secondary outcomes are documented. For groups 5 and 6 (PDR requiring vitrectomy: placebo and levosulpiride), there is only one visit 1 week after enrollment, i.e., at the time of vitrectomy.

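### Missing outcome data is a reason to eliminate a randomised patient, although most groups have outcomes recorded at three or four visits; the power cost so far is small, but the exclusion can bias the comparison.

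*Protocol article*

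**What the plan says.** Under Eligibility Criteria, the article lists seven Elimination Criteria. The last is missing outcome data. It does not say which outcome, how many visits, or whether some post-baseline data would keep the patient in.

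Current Status reports the rule applied. Among the nine patients who dropped out after randomisation, the entry is "2 missed outcome data", beside three for non-compliance with study medication, one for conventional therapy and three for rescheduled vitrectomy. It then says that "45 completed the study".

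Outcome Measures sets the visit schedule:
- Groups 1-4: "four study visits take place every 2 weeks during a follow-up period of 8 weeks".
- Groups 7-8: "enrollment is followed by three visits, one every 4 weeks".
- Groups 5-6: "there is only one visit 1 week after enrollment".

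For the repeated-visit groups it adds: "At each visit, the medical history, physical examination, adverse events, and primary and secondary outcomes are documented".

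Sample Size names elimination of patients among the reasons why the sample size may have to change. Enrollment and Randomization has one rule that keeps a result for a patient who stops: stopping for intolerable adverse effects is reported as a failure. That rule does not cover missing outcomes.

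**The concern.** The criterion acts on the patient, while what is missing may be a single value. A patient in groups 1-4 who misses one visit, or one fluorescein angiogram, can still have visual acuity and retinal thickness from up to three or four other occasions. If that patient is eliminated, these observations are lost to the comparison.

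Two things are at stake. The first is precision: with 120 patients over eight arms, each arm is small. The second matters more. Missing an outcome happens after randomisation, so excluding patients for it means that the arms compared are no longer the arms randomised. If patients who do badly or tolerate treatment poorly are more likely to miss an assessment, and this differs between levosulpiride and placebo, the difference among those who remain is biased, even though earlier visits may already show how the excluded patients were doing.

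**Working it through.** **1. Reproduce the article's counts.** From Current Status: 3 + 2 + 1 + 3 = 9 drop-outs, and 54 − 9 = 45 completers. All 54 are accounted for. The share lost for missing outcomes is 2/54 = 3.7%, against 9/54 = 16.7% for all reasons.

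**2. Does the wording remove patients from the analysis?** Three places bear on it:
- Elimination Criteria: missing outcome data is a reason for elimination.
- Current Status: the two patients are counted as dropped out and are set against those who completed.
- Sample Size: elimination is treated as a loss that may require a different sample size.

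Together these point to loss from the analysis. No section names an analysis set, and none says that earlier visits of eliminated patients are used. The step is therefore an inference, though a consistent one.

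**3. Where could partial data exist?** Groups 1-4 have four post-enrolment visits, groups 7-8 three, and groups 5-6 one. In groups 5-6 a missing outcome leaves no other visit, although one assay may be available without the other. The groups of the two patients are not given.

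**4. Power cost at the observed rate.** Inputs from Sample Size: difference 10 letters, SD 10, type I error 5% (two-sided assumed). The size per arm is in a figure that is not shown, so I assume an equal split, 120/8 = 15. After a 3.7% loss, 15 × 52/54 = 14.4 per arm.

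Normal approximation: power = Φ(√(n/2) × 10/10 − 1.96).
- n = 15: Φ(2.739 − 1.960) = 78.2%
- n = 14.4: Φ(2.687 − 1.960) = 76.7%, a loss of 1.5 points

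The two-sample t-test gives 75.3% and 73.6%, a loss of 1.7 points.

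For scale, removing all nine types of loss leaves 15 × 45/54 = 12.5 per arm and 70.5% power (normal approximation). Most of that fall comes from the other reasons for dropping out.

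**5. How large could the bias be?** The documents give no missingness mechanism, so this is an illustrative extreme. Suppose that a fraction f of one arm is removed, that these are its worst responders, and that nobody is removed from the other arm. With a normal outcome and SD 10, that arm's mean shifts by 10 × φ(c)/(1 − f), where c is the f-quantile of the standard normal.
- f = 2/54 = 3.7%: c = −1.786, 10 × 0.0809/0.963 = 0.8 letters
- f = 2/27 = 7.4% (both losses in one of two pooled arms of 27): c = −1.446, 10 × 0.1402/0.926 = 1.5 letters

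These compare with the 10-letter difference used for planning. The real bias could be anywhere from nil to about this size at the present rate, and more if missingness rises.

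**The case against.** The strongest counter-argument is that the analytic consequence is not written down. Elimination may mean only that participation ended, Current Status reports participant flow and not an analysis, and analysis sets are often left to a full protocol or an SAP that is not shown. This stands in part: the exclusion is inferred. It does not remove the point, because the article itself states the criterion, reports it as applied, and treats elimination as a loss to sample size.

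A reader might go further and infer three things that the article does not support.

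- **That any single missed visit triggers elimination.** On that reading, a 5% miss rate per visit would remove 1 − 0.95⁴ = 18.5% of groups 1-4, and a 10% rate 1 − 0.90⁴ = 34.4%. No section states such a trigger, and the observed figure is 3.7%. The 34.4% would also exceed the expected total dropout of under 20% in Study Setting and Sample.
- **That a large bias has been shown.** If patients who have lost more than 5 letters at week 6 miss week 8 half the time, or always, the completers' difference falls from 10 letters to about 9.1 or 7.8 (correlation 0.7 between visits). But these scenarios remove about 10% and 21% of patients. Scaled to 3.7%, the same mechanism gives about 9.8 letters. Worsening that needs conventional treatment also has its own, separate criterion.
- **That safety data are discarded.** Nothing says so. Adverse events are documented at every visit, and Dissemination promises that all data, including adverse events, will be communicated.

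It is also fair to say that the two patients may have no post-baseline values, and that other elimination criteria, non-compliance among them, account for more of the losses.

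**Conclusion.** The point holds in limited form. The article fixes a post-randomisation elimination rule with no threshold, has applied it to 2 of 54 randomised patients, and does not reconcile it with repeated outcome recording in groups 1-4 and 7-8. For groups 5-6 it has little practical effect.

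The power cost of this criterion alone is about 1.5 to 2 points at the observed rate, given an equal split of 15 per arm, a two-sided 5% test, and 10 letters with SD 10. Power is not the main reason to act. The reason is that excluding randomised patients for a later event can bias the comparison if missingness is related to outcome and differs by arm. The documents do not determine how much; my extreme case at the present rate is about 0.8 to 1.5 letters.

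The conclusion rests on reading elimination as removal from the analysis. If the full protocol or SAP says that these patients' data are kept, a clarifying sentence is all that is needed. The rule would otherwise govern the rest of the planned 120 patients, so it should be changed now.

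**What to change.** - Delete missing outcome data as a reason to remove a patient.
- For repeated quantitative outcomes in groups 1-4 and 7-8, such as visual acuity and OCT thickness, analyse randomised patients in the arm allocated, using all observed visits. A mixed model for repeated measures would serve, with arm, visit, arm by visit and the baseline value, and the end-of-treatment contrast as the estimate.
- For single-time outcomes (vitreous PRL and vasoinhibins) and qualitative ones, where such a model is not suited, use all available values.
- State that the safety records of these patients are reported.
- Restore the two patients to every outcome for which they have post-baseline data, and say so if they have none.

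The cost is one deleted criterion and a few sentences of analysis wording, with no new visits, measurements or patients. The small downside is that the mixed model assumes data missing at random, so a completers analysis should be kept as a sensitivity analysis.
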